**Clinically relevant individual outcomes (n=56):**
Abdominal aortic aneurysm repair/aortic bypassAchilles tendon ruptureAll-cause mortality (prespecified)ArthroscopyAsthmaAtrial fibrillation/flutter or other arrhythmia (pacemaker insertion, palpitations, tachycardia unspecified, atrioventricular block, supraventricular tachycardia, or other conduction disorders)Bowel obstructionBradycardiaBronchoscopyCarotid endarterectomyCarotid ultrasoundCataract, unspecifiedChest X-rayCholecystitis, unspecifiedClostridium difficile colitisColposcopyComputed tomography: abdomenComputed tomography: headComputed tomography: thoraxCutaneous drug reactionCystoscopyDepressionDisorders of calcium metabolismEmergency department visit for any reason (prespecified)GoutGuillain-Barré syndromeHead traumaHearing lossHospital admission for any reason (prespecified)HyperkalemiaHypoglycemiaHypokalemiaHyponatremiaIntensive care unit admissionKidney stonesLaparoscopyLiver disease toxicityLower limb amputationMajor abdominal surgeryMajor cardiovascular surgeryOsteoarthritisPancreatitisParkinson’s diseasePhysician visit for any reason (prespecified)PneumoniaRenal biopsyRetinal detachmentRhabdomyolysisRheumatoid arthritisSelf-harmSepsisSurgery (for any reason other than major abdominal surgery, major cardiovascular surgery, lower limb amputation and fracture, and major ortho procedure)Severe respiratory depressionUrinary incontinenceUrinary retentionVenous thromboembolism
**Clinically relevant composite outcomes (n=18):**
Acute dialysis or acute kidney injuryAplastic anemia (unspecified), neutropenia, or other agranulocytosis, or thrombocytopenia (unspecified)Cardiac arrest or ventricular arrhythmiaCardiac catheterization or coronary revascularizationColonoscopy or esophagogastroduodenoscopyDiabetic ketoacidosis, hyperglycemia, or hyperosmolar nonketotic comaDelirium or other encephalopathyDelirium, fall, or other encephalopathyEchocardiography or Holter monitoringElectroencephalography or seizuresEmergency department visit or hospital admission for any reason (prespecified)Fall, fracture or major orthopedic procedure, or fractureFall or hypotensionFall or syncopeHeart failure or myocardial infarction (most-responsible diagnosis), or ischemic stroke (most-responsible diagnosis)Hemarthrosis or hemorrhage (not elsewhere classified), intracerebral hemorrhage (unspecified), lower gastrointestinal bleed, other nontraumatic intracranial hemorrhage, subarachnoid hemorrhage (unspecified), or upper gastrointestinal bleedingHypotension or syncopeUrinary tract infection or urine culture

### Statistical Analysis Plan

All analyses will be programmed and automated using Python, SAS, the JavaScript library D3, and R (R Foundation for Statistical Computing) and will be conducted on the Health Artificial Intelligence Data Analytic Platform, a high-performance computing environment for analyzing ICES data. The open source JavaScript library D3 will be used to develop interactive visualizations.

#### Analysis to Balance the Exposed and Referent Groups in Each Cohort

Propensity scores will be calculated using multivariable logistic regression, incorporating more than 400 baseline characteristics (the complete list and coding definitions are provided in Multimedia Appendix 2). Characteristics include calendar year, prior use of drug A, demographics (eg, age, sex, neighborhood income quintile, urban vs rural residence, geographic region [31], and long-term care home residency), comorbidities (eg, asthma, diabetes, coronary artery disease) assessed over the 5 years before cohort entry, health care use in the year prior (eg, hospitalizations, emergency room visits, specialist consultations), and prescription drug dispensing within 120 days before cohort entry. The 120-day lookback period accounts for potential delays in prescription refills, ensuring comprehensive capture of medication dispensing.

The propensity scores will estimate the probability of a patient being in the exposed group versus the referent group, given their baseline characteristics. To enhance the comparability of the exposed and referent groups, we will exclude (1) individuals in the referent group with propensity scores lower than the lowest 1% of scores in the exposed group and (2) individuals in the exposed group with propensity scores higher than the highest 99% of scores in the referent group. This will also ensure that we do not violate the positivity assumption in causal inference, which requires that there should be a nonnull probability across each stratum of baseline characteristics within both the exposed and referent groups [32].

Inverse probability of treatment weighting (IPTW) using average treatment-effect-in-the-treated (ATT) weights will then be used to balance the exposed and referent groups on baseline characteristics as follows: Individuals in the referent group will be weighted using ATT weights, defined as their odds of being in the exposed group (propensity score/[1 − propensity score]). Individuals in the exposed group (the medication pair group) will receive weights of 1. This method will produce a weighted pseudosample of individuals in the referent group with a distribution of measured characteristics similar to that of the exposed group [33,34]. Between-group differences in baseline characteristics in the weighted samples will be examined using standardized differences (SDs) [35].

Cohorts will be excluded from further analysis if fewer than 95% of the baseline characteristics are balanced between the exposed and referent groups (ie, the SDs must be <10% for ≥95% of the characteristics).

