#### Cohort Entry Dates for Exposed and Referent Groups

The exposed group will comprise regular users of drug A and new users of drug B, as described earlier. The cohort entry date for individuals in the exposed group will be the start date of drug B. The referent group will comprise regular users of drug A who are not coprescribed drug B. The cohort entry date for individuals in the referent group will be assigned based on the distribution of the time differences between the most recent prescription for drug A and the initiation of drug B for individuals in the exposed group, ensuring similar observation periods between groups [25].

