#### Individual-Level Exclusion Criteria Applied to the Exposed and Referent Groups

We will exclude individuals who meet any of the following criteria:

Individuals prescribed drug B within 180 days before the cohort entry date (to ensure those in the exposed group are new users of drug B and that those in the referent group were not previously exposed).Individuals prescribed another medication in the same class as drugs A and B on the cohort entry date. For example, if drug A or B is sertraline, which is a serotonin reuptake inhibitor (SSRI), individuals prescribed a nonsertraline SSRI on the cohort entry date will be excluded.Individuals discharged from the hospital or emergency department within 2 days before the cohort entry date (to ensure that prescriptions are new outpatient prescriptions).Individuals whose day supplies for drug A or B are ≥100 days or <2 days.Individuals who are nonpermanent Ontario residents, are aged <66 or >105 years on the cohort entry date, or have a date of death on or before the cohort entry date (data cleaning exclusions).

An individual can only enter a cohort once; if an individual meets the eligibility criteria multiple times, the first eligibility date will serve as the cohort entry date.

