### Outcomes

We will examine 74 outcomes within 30 days of cohort entry (Textbox 1). The outcomes were chosen using a prespecified analytic approach and considering the clinical significance of the outcomes and the observed rates in the study region [16]. Many of the algorithms used to identify these outcomes have been validated in previous studies and demonstrate high sensitivity and specificity [26-30]. Shorter and longer follow-up times for outcomes will be examined in additional analysis (see the *Additional Analysis to Characterize the Signals* section).

Final set of 74 clinically relevant outcomes (ordered alphabetically).

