Survival analysis. To assess whether the initial signal persists when analyzed using a time-to-event approach, we will conduct a Cox proportional hazards regression with a 30-day follow-up period, censoring on death when all-cause mortality is not the outcome of interest. We will test the proportional hazards assumption by including an interaction term between the new-user status and follow-up time. This analysis will help determine whether the signal is robust across different modeling techniques.Negative-control exposure analyses. To detect potential biases from unobserved confounders, we will perform negative-control exposure analyses. A negative-control exposure is a variable that shares the same sources of bias as the drug of interest but cannot plausibly cause the outcome. We will rerun the regression analyses for the initial signals using a control exposure period starting 90 days before cohort entry [37]. This analysis will help identify any confounding factors that may have influenced the initial signal. Notably, the outcome of all-cause mortality cannot be examined with this method, as all patients lived to their cohort entry date. A positive association (ie, RRs and RDs significantly different from null, with *P*<.05) in this analysis would suggest potential confounding, whereas the absence of an association would bolster the credibility of the original signal.E-value analysis. We will conduct E-value analyses to quantify the minimum strength of association an unmeasured confounder would need to have with both the drug combination and the outcome to negate the observed signal [38]. Larger E-values indicate that substantial unmeasured confounding would be required to explain away the signal, whereas smaller E-values suggest that minimal unmeasured confounding could do so. For an initial signal to be considered robust, the E-value must exceed 2.Propensity score matching. To further validate the robustness of the signal, we will use 1:1 propensity score matching to balance the exposed and referent groups on baseline characteristics [39]. This method estimates the average treatment effect in the treated and mitigates the influence of extreme weights, which can occur with IPTW. Consistency between the results of this analysis and the initial findings will strengthen the validity of the signal.Bootstrap analysis. We will use a multiplier bootstrap procedure to compute RRs and RDs across 200 random samples, each of the same size as the original cohort. This method helps correct SEs and CIs, ensuring they have the correct coverage rates [36,40]. For the signal to be considered robust, at least 90% of the bootstrap samples must yield results consistent with the original findings, with *P*<.05 and CIs for RRs and RDs in the same direction as initially observed.

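### As described, hospital and emergency use is balanced over the prior year without a stated recency term, so groups can match on use yet differ in time since discharge, which can bias RR and RD upward in cohorts where drug B often follows a discharge

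*Protocol article*

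**What the plan says.** All of the following is in the Methods of the protocol article.

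- **Covariates** (Analysis to Balance the Exposed and Referent Groups): each domain has its own look-back. Comorbidities use 5 years, utilisation is "health care use in the year prior (eg, hospitalizations, emergency room visits, specialist consultations"), and medication is "prescription drug dispensing within 120 days before cohort entry". The full list of more than 400 items is in Multimedia Appendix 2.
- **Balance rule** (same section): "the SDs must be <10% for ≥95% of the characteristics".
- **Entry dates** (Cohort Entry Dates): "The cohort entry date for individuals in the exposed group will be the start date of drug B". Referent dates are "assigned based on the distribution of the time differences between the most recent prescription for drug A and the initiation of drug B".
- **Exclusion** (Individual-Level Exclusion Criteria): "Individuals discharged from the hospital or emergency department within 2 days before the cohort entry date". The stated purpose is to make sure that the prescriptions are new outpatient ones.
- **Outcomes**: "We will examine 74 outcomes within 30 days of cohort entry".
- **Signal criteria**: the lower 95% limit must be at least 1.33 for the RR and at least 0.1% for the RD, and both P values must survive Benjamini-Hochberg.
- **Negative control** (Sensitivity and Bias Analyses): the models are rerun with "a control exposure period starting 90 days before cohort entry". The plan itself notes that this cannot be done for all-cause mortality.

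**The concern.** Starting a new drug is a clinical decision that may follow an admission or emergency visit. A referent date drawn from the gap after a drug A fill has no such event behind it. A one-year utilisation variable, whether coded as yes/no or as a count, gives the same value to a discharge 5 days ago and one 11 months ago. Weighting can equalise it while the exposed group remains more recently ill.

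Several of the 74 outcomes could plausibly be driven by recent acute illness: death, any admission, emergency visit, intensive care, sepsis, delirium, falls and acute kidney injury. The excess would be baseline risk carried through the 30 days and could be read as harm from the pair. Benjamini-Hochberg controls chance findings; it does nothing about a systematic shift.

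**Working it through.** The plan gives no figure on this point, so there is none to reproduce. The model below assumes perfect balance on prior-year hospitalization and no drug effect. All risks and shares are assumptions.

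**1. Referent timing.** If a single discharge falls evenly over days 3-365 before entry, the share in days 3-30 is 28/363 = 7.7%, and the mean time since discharge is (3 + 365)/2 = 184 days. With two or three independent stays, the share with a discharge in days 3-30 is 1 - (1 - 0.0771)^2 = 14.8% or 1 - (1 - 0.0771)^3 = 21.4%.

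**2. Null RR.** Risk = h[s·a + (1 - s)·b] + (1 - h)·c. Here h is the share hospitalized in the year, s the share of those discharged in days 3-30, and a, b, c are the 30-day risks for recent discharge, earlier discharge and none.

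Take h = 20% in both groups, a/b/c = 20%/4%/1%.

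- Referent, s = 7.7%: 0.2 × (0.0771 × 0.20 + 0.9229 × 0.04) + 0.8 × 0.01 = 1.85%.
- Exposed, s = 20%: 0.2 × (0.040 + 0.032) + 0.008 = 2.24%. RR 1.21, RD 0.39%.
- Exposed, s = 30%: 0.2 × (0.060 + 0.028) + 0.008 = 2.56%. RR 1.39, RD 0.71%.
- Exposed, s = 50%: 0.2 × (0.100 + 0.020) + 0.008 = 3.20%. RR 1.73, RD 1.35%.

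With a weaker gradient (15%/5%/1.5%) the three RRs are 1.10, 1.19 and 1.36. With 10%/5%/3% they are 1.04, 1.06 and 1.12. At h = 10% and s = 30% the first two gradients give 1.25 and 1.12.

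**3. Referents with several stays.** Steep gradient, h = 20%: at s = 30% the RR of 1.39 falls to 1.23 (two stays) or 1.12 (three). At s = 50% the RR of 1.73 falls to 1.54 or 1.40.

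**4. Against the signal thresholds.** These are lower limits, not point estimates. I used four referents per exposed person and unweighted variances; variable weights would normally widen the limits.

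| Case | Exposed | Lower RR | Lower RD |
|---|---|---|---|
| RR 1.73 | 583 | 1.01 | -0.18% |
| RR 1.73 | 3,000 | 1.37 | 0.68% |
| RR 1.73 | 5,000 | 1.44 | 0.83% |
| RR 1.39 | 583 | 0.77 | -0.68% |
| RR 1.39 | 100,000 | 1.326 | 0.61% |

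The Results section reports a median of 583 new users per initial cohort (IQR 237-2130). Its examples include cohorts of 2702, 4220, 128,762 and 197,057 patients. Only the strong case passes both thresholds, and it needs more exposed people than the upper quartile.

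**5. Planned safeguards.** With a 30-day window (assumed, since only the start is stated), the negative-control period covers about day -90 to day -60, before an illness in the last weeks. Cox regression, matching and bootstrap, as described, use the same groups and baseline characteristics. The E-value rule adds little, because an RR of 1.33 already gives 1.33 + √(1.33 × 0.33) = 1.99 against the required 2. Agreement in both directions can share the bias, since either drug may be started after an acute episode.

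**6. After balancing recency.** With the same s in both groups, the model returns RR 1.00 and RD 0.

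**The case against.** The strongest objection is that the covariate list is not shown. The utilisation items are introduced as examples, and Appendix 2 may contain a recent-discharge variable. That stands: it cannot be said that use is balanced only over a year. But the article does state a window for this domain, and that stated choice is what is questioned here.

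A reader might infer that every cohort in which B tends to follow discharge will produce a false signal, or that the RD threshold is easily passed. Neither is supported. Both criteria apply to lower limits. At the median of 583 exposed even the RR 1.73 case fails both, and the RR 1.39 case stays below 1.33 at 100,000 exposed.

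The even-timing, single-stay assumption for referents also favours the concern. The first eligible date is used, so some referents may enter soon after beginning drug A, itself perhaps started around an illness. The 120-day dispensing covariates are a partial proxy for recent illness and are given no effect in the model. Both would shrink the bias.

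Saying that the negative control cannot detect the bias would also go too far. The end of its window is not stated; one that ran closer to entry could pick up recent stays.

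Finally, the 2-day exclusion removes the most recent discharges, the limitations concede residual confounding, and signals pass through external-evidence review before any action. These soften the consequences but do not address discharges from day 3 onward.

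**Conclusion.** The concern holds in limited form. As described, the design lets time since discharge differ between groups that balance on prior-year use. The bias is upward in cohorts where B is often started soon after discharge. With 20% hospitalized in both groups and the two steeper gradients, the null RR is about 1.1 to 1.7. It is less if referents have several stays or if the dispensing covariates capture part of the difference.

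A false signal from this source alone needs strong recency imbalance, a steep gradient and a cohort of some thousands. That is plausible for some of about 200,000 pairs by 74 outcomes, not for pairs in general. Weaker bias still inflates estimates and can help a modest association over the thresholds. The conclusion rests on the assumed risks, on a 30-day negative-control window and on Appendix 2 having no recency term.

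**What to change.** Unless Appendix 2 already has them, add indicators of hospital discharge and of emergency visit within 30 days and within 31-90 days before entry to the propensity score. Report their standardized differences for each flagged signal; they need not form a separate exclusion rule for cohorts.

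Rerun each flagged signal after excluding, in both groups, anyone discharged from hospital or emergency department within 30 days before entry. Treat a signal whose RR moves materially toward 1 as not supported. Define in advance what counts as material, and judge it on the point estimate, because the smaller sample will widen the interval anyway.

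The cost is four more covariates from databases already linked, one rerun per flagged signal, and some loss of precision.

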#### Criteria for Identifying Potential Signals of Harmful DDIs

Associations between a drug pair and an adverse outcome that meet the following criteria will be considered potential signals of harm and analyzed further:

Thresholds for RRs and RDs. The lower bound of the 95% CI for the RR must be ≥1.33, and for the RD, it must be ≥0.1%. These thresholds were chosen to ensure that only clinically significant increases in risk (of sufficient magnitude to be of concern) are considered. This analysis will focus solely on potential harms from drug combinations rather than protective benefits.Statistical significance. The *P* values from the modified Poisson regression model (for RRs) and the binomial regression model (for RDs) must be statistically significant after applying the Benjamini-Hochberg correction. This correction accounts for multiple comparisons across all outcomes and drug pair cohorts. The false discovery rate will be set at 5%, and the highest *P* value below the Benjamini-Hochberg critical value will be considered statistically significant, along with all *P* values below it. This correction will minimize the risk of false-positive discoveries (type I errors).

Drug pair cohorts that do not generate significant signals will not undergo further analysis.

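### A drug of another class first dispensed on the same day as drug B appears neither excluded nor balanced, so its harm can be reported as an A+B signal

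*Protocol article*

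**What the plan says.** All references are to the protocol article.

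- **Time zero, exposed** (Cohort Entry Dates for Exposed and Referent Groups): "The cohort entry date for individuals in the exposed group will be the start date of drug B". Every exposed person therefore has a new dispensing on day 0.
- **Time zero, referents** (same section): "The referent group will comprise regular users of drug A who are not coprescribed drug B". Their date is "assigned based on the distribution of the time differences between the most recent prescription for drug A and the initiation of drug B". Nothing requires a new drug on that date, and nothing forbids a drug other than B.
- **Other drugs on the entry date** (Individual-Level Exclusion Criteria): the one relevant rule removes "Individuals prescribed another medication in the same class as drugs A and B on the cohort entry date".
- **Drug covariates** (Analysis to Balance the Exposed and Referent Groups in Each Cohort): "prescription drug dispensing within 120 days before cohort entry". The full list and coding are in Multimedia Appendix 2, which is not shown.
- **Signal rule** (Criteria for Identifying Potential Signals of Harmful DDIs): "The lower bound of the 95% CI for the RR must be ≥1.33", together with a lower bound of at least 0.1% for the risk difference and significance after the Benjamini-Hochberg correction.
- **Checks required of a signal** (Sensitivity and Bias Analyses): Cox regression, a negative-control analysis "using a control exposure period starting 90 days before cohort entry", an E-value condition ("the E-value must exceed 2"), 1:1 matching and a bootstrap.

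**The concern.** Drugs are often started together, for instance as a combination course or as several new prescriptions after one visit. The same-class exclusion shows that the plan already treats other drugs taken on day 0 as a threat, but it covers only part of it. A third drug C, from another class and first dispensed with B, passes the exclusions. Read literally, it also falls outside a covariate window that ends before entry.

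If C starts on day 0 more often among the exposed than among referents, and C (alone or with A) raises the 30-day risk of an outcome, the A+B contrast carries that risk even when B is harmless. This is not confounding by B's indication or B's own toxicity: the association is real, but the wrong drug is named. Control of the false discovery rate deals with chance and does not help. The study aims at credible signals for specific pairs among about 200,000, so naming the wrong pair goes to the heart of the output.

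**Working it through.** The plan gives no figure on this point, so there is none to reproduce. The check has three parts.

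**1. Does any required check detect a day-0 start of C?**

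- Cox regression and the bootstrap reuse the same groups.
- Matching balances the same baseline characteristics.
- The negative-control window opens 90 days before entry. A patient whose first dispensing of C is on day 0 was not taking it then, so a null result there would wrongly support the signal.
- E-value: E = RR + √[RR(RR − 1)]. At RR = 1.33, E = 1.99. At RR = 1.333, E = 2.00. A signal whose lower bound has reached 1.33 has in effect already met the condition.
- The bidirectional comparison (A added to B as well as B added to A) is highlighted where concordant, but it is not a requirement.

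**2. How large is the bias?**

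Let p1 and p0 be the shares of exposed and referents who start C on day 0, and RRc the risk ratio for C. With no true A+B effect:

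apparent RR = [1 + p1(RRc − 1)] / [1 + p0(RRc − 1)]

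The documents give none of these three inputs; the values below are assumptions.

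| p1 | RRc | p0 = 0.5% | p0 = 2% | p0 = 5% |
|---|---|---|---|---|
| 5% | 2 | 1.04 | 1.05/1.02 = 1.03 | 1.00 |
| 20% | 3 | 1.39 | 1.40/1.04 = 1.35 | 1.27 |
| 30% | 3 | 1.58 | 1.60/1.04 = 1.54 | 1.45 |
| 50% | 2 | 1.49 | 1.50/1.02 = 1.47 | 1.43 |
| 30% | 5 | 2.16 | 2.20/1.08 = 2.04 | 1.83 |

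The co-start share at which the point estimate alone reaches 1.33 is p1 = [1.33(1 + p0(RRc − 1)) − 1]/(RRc − 1). At p0 = 2% this is 36% for RRc = 2, 19% for RRc = 3, 11% for RRc = 5 and 7% for RRc = 8.

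**3. How often would the lower bound reach 1.33?**

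Probability ≈ Φ{[ln RR − ln 1.33]/SE − 1.96}, with SE² = (1 − r1)/(n1·r1) + (1 − r0)/(n0·r0) and r1 = r0·RR.

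From the Results section: the median is 583 new users per cohort, with upper quartile 2130. Assumed: four referents per exposed person, baseline 30-day risk r0 of 1% or 3%, and 20,000 exposed to represent a large cohort.

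Example: n1 = 583, n0 = 2332, r0 = 3%, RR = 2.037, so r1 = 6.11%. SE = √(0.0264 + 0.0139) = 0.2005. (0.7115 − 0.2852)/0.2005 − 1.96 = 0.17, and Φ(0.17) = 0.57.

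| Apparent RR | 583 exposed (1% / 3% risk) | 2130 exposed | 20,000 exposed |
|---|---|---|---|
| 1.35 | 0.03 / 0.03 | 0.03 / 0.03 | 0.04 / 0.05 |
| 1.54 | 0.06 / 0.10 | 0.11 / 0.24 | 0.59 / 0.97 |
| 2.04 | 0.23 / 0.57 | 0.64 / 0.98 | 1.00 / 1.00 |

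In every cell the risk-difference bound is met at least as often. The figures ignore the loss of precision from weighting and the Benjamini-Hochberg step, so they are upper estimates of the chance of passing all criteria.

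**The case against.** **Day-0 coverage is not known.** Whether the 120-day window includes the entry date is a coding detail that an article may leave to its appendix. If it does, the score carries C. This stands, and it is why the point is conditional. It is not a full answer, though: an indicator of any dispensing in the window would not separate a first dispensing on day 0 from established use, and the balance rule tolerates imbalance in up to 5% of characteristics (0.05 × 400 = 20).

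**Referents may also start drugs on their date.** A reader might infer that no referent starts anything on the assigned date. The protocol does not say so. Referent dates follow the exposed group's gap since the last drug A fill. That gap may be zero, so some referents are dated on a fill day, when other drugs may also be started. This stands: p0 is not zero, and an excess among the exposed is likely but not documented.

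**A point estimate of 1.33 is not the rule.** This stands. An apparent RR of 1.35 hardly ever passes, and one of 1.54 seldom passes at the median cohort size. It would be tempting to say that one harmful A-C pair produces a false signal for every B co-started with C, or that such signals pass every check. The thresholds do not support that.

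**Other safeguards exist.** Excluding discharges within the previous 2 days removes one source of multi-drug starts. In the reverse initiation order, a B-C co-start is no longer tied to time zero. Signals also go through pharmacological and literature review by two reviewers, who may dismiss an implausible pair. All three reduce the problem. But outpatient co-starts remain, the reverse comparison is not required, and the review concerns the named pair, with no step that asks what else the exposed started. Conflicting evidence would lead to a further study of the wrong pair.

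**Conclusion.** The gap holds on the text, subject to the unseen appendix. A drug C of another class first dispensed on the entry date is neither excluded nor stated to be balanced, and no required check is aimed at it. C's effect can therefore be reported as an A+B signal; the documents do not show that it will be.

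The size depends on assumed inputs. With 2% of referents starting C, the apparent RR runs from 1.03 (5% of exposed, RRc = 2) through 1.35 and 1.54 (20% and 30%, RRc = 3) to 2.04 (30%, RRc = 5). Given the lower-bound rule, the risk is concentrated in large cohorts with common co-starts of a strongly harmful C. The Results section describes example cohorts of 128,762 and 197,057 patients, so cohorts large enough for imprecision to give little protection do occur. For rare co-starts or a weak C the bias is negligible.

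**What to change.** For signals only, add one analysis to the section on sensitivity and bias analyses:

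- Repeat the weighted RR and RD after excluding, from both groups, anyone with a first dispensing (none in the prior 180 days) of any drug other than A or B on the cohort entry date. With such starters removed from both groups, p1 = p0 = 0 and the bias factor is 1.00 under the model above.
- Report the share of each group that co-started another drug.
- Where the estimate attenuates materially, or too few sole starters remain, label the signal as A + B started together with C, and name C. This is preferable to a strict pass/fail rule on the reduced sample, where a wider interval alone could remove a true signal.

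Also state, in the paragraph on the propensity score, whether the 120-day covariate window includes day 0.

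The cost is one restricted rerun per signal on dispensing data already held. The downside is fewer exposed patients and wider intervals for pairs usually started alongside other drugs.

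### Each propensity-score cut-off trims one group only, so exposed and weighted referents end on different score ranges and RRs and RDs are biased wherever outcome risk varies with the score

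*Protocol article*

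**What the plan says.** All of this stands in the protocol article, under Analysis to Balance the Exposed and Referent Groups in Each Cohort. Two exclusions are listed. The lower one removes "individuals in the referent group with propensity scores lower than the lowest 1% of scores in the exposed group". The upper one removes "individuals in the exposed group with propensity scores higher than the highest 99% of scores in the referent group", read here as scores above the referents' 99th percentile. Of the trimming the section then says: "This will also ensure that we do not violate the positivity assumption in causal inference".

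The remaining referents receive ATT weights, "defined as their odds of being in the exposed group (propensity score/[1 − propensity score"), and "Individuals in the exposed group (the medication pair group) will receive weights of 1". The stated result is: "This method will produce a weighted pseudosample of individuals in the referent group with a distribution of measured characteristics similar to that of the exposed". A cohort proceeds only if "the SDs must be <10% for ≥95% of the characteristics".

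Nothing in the article removes referents above the upper cut-off, truncates weights, or re-estimates the score after trimming.

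**The concern.** The weight PS/(1 − PS) rises with the score, so the top 1% of referents are the most heavily weighted people in the analysis. Their weight is there to reproduce the exposed patients in the same score range, and the upper exclusion deletes exactly those patients. That range is left with heavily weighted referents and no exposed, which is the lack of overlap the trimming was meant to prevent. At the lower end the mirror fault occurs: up to 1% of exposed stay after the referents in that range have gone. This effect is small.

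If the characteristics that lead to drug B also raise outcome risk, the referent risk is too high for the exposed group that remains, and a real harm can fall below the signal thresholds (lower confidence bound of 1.33 for the RR and 0.1% for the RD). If they lower the risk, the error runs toward false signals. The same rule would be applied automatically to every cohort and up to 74 outcomes in each.

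**Working it through.** The article gives no figure for this step, so there is none to reproduce. It also gives neither the separation of the scores nor the slope of outcome risk on the score. Both are assumed below and varied.

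**Large-sample calculation.** Let x be the logit score in SD units.

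- Referents: x ~ N(0,1). Exposed: x ~ N(s,1). ATT weighting turns the referent distribution into N(s,1), so without trimming the groups match.
- Upper cut-off U = 2.326 (referent 99th percentile). Lower cut-off L = s − 2.326 (exposed 1st percentile).
- As written, exposed are kept for x < U and weighted referents for x > L.
- Share of exposed deleted = 1 − Φ(2.326 − s).
- Share of the remaining referent weight lying above U = [1 − Φ(2.326 − s)] / 0.99.
- With risk proportional to exp(bx) and a true RR of 1:

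  RR = [Φ(2.326 − s − b)/Φ(2.326 − s)] × [0.99/Φ(2.326 + b)]

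The first factor is the upper tail and the second the lower tail. For s = 1.0 and b = 0.5: 0.877 × 0.992 = 0.870. Nearly all of the bias comes from the upper tail.

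| s (c-statistic) | exposed deleted | referent weight above U | RR, b = 0.1 | b = 0.2 | b = 0.3 | b = 0.5 | b = −0.3 |
|---|---|---|---|---|---|---|---|
| 0.5 (0.64) | 3.4% | 3.4% | 0.99 | 0.98 | 0.96 | 0.93 | 1.03 |
| 1.0 (0.76) | 9.2% | 9.3% | 0.98 | 0.95 | 0.93 | 0.87 | 1.06 |
| 1.5 (0.86) | 20.4% | 20.6% | 0.96 | 0.92 | 0.88 | 0.78 | 1.11 |

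For b = 0 both factors equal 1, so there is no bias. At s = 1.0 a true RR of 1.60 would read 1.60 × 0.870 = 1.39 with b = 0.5, and 1.60 × 0.929 = 1.49 with b = 0.3.

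**Simulation with a fitted score.** Setting: 30,000 people, 40 covariates, a logistic propensity model, outcome log-odds slope 0.4 per SD, true RR 1, and SD of the exposure linear predictor 0.5, 1.0 and 1.5.

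- Rule as written: RR 0.95, 0.92 and 0.90; RD −0.13, −0.24 and −0.33 percentage points. These RD errors exceed the protocol's 0.1% RD threshold.
- Slope −0.4: RR 1.04, 1.06 and 1.09.
- Middle separation, slope 0.4, one tail at a time: upper exclusion alone 0.929, lower alone 0.994, both 0.923.
- Score re-estimated after the one-group trim (middle separation): 0.923 becomes 0.971 at slope 0.4, and 0.850 becomes 0.930 at slope 0.7.
- Both groups trimmed at both cut-offs: RR 0.992 to 1.004 in every scenario.

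**Balance criterion.** It looks at covariates one at a time, whereas the shift is spread over all of them.

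- 40 covariates: on average 94% to 100% still had a standardized difference under 10%.
- 100 covariates, slope 0.4: 100% did, with RR 0.95, 0.90 and 0.84 at the three separations (0.99, 0.96 and 0.92 with the score refitted).
- 20 covariates, slope 0.5: 100%, 100% and 71–81%, so at the largest separation the criterion would usually have excluded the cohort.

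**The case against.** A reader might infer that every RR and RD in the study is biased. The documents do not support that. The bias is exactly zero for an outcome whose risk does not vary with the score, and the score includes items such as calendar year and region that may predict drug B without a steep outcome gradient. At a slope of 0.1 the bias is about 1% to 4%. Nor do the documents support any single figure for its size, since they give neither separation nor slope.

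The balance criterion does offer some protection: in the 20-covariate simulation it would have removed most cohorts at the largest separation. That does not carry over to many covariates, where the shift per covariate is thinner and the criterion passed.

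The score may be re-estimated after trimming. The article does not say, and its appendix on analytic steps is not shown. This would shrink the bias but leave part of it.

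Later checks also count. Signals must be supported by sensitivity analyses that include 1:1 propensity matching, which does not place extreme weights on high-score referents, so a false signal from this source can be caught. This part of the objection stands. It does not help with missed harms: matching is run only on associations that already met the signal criteria, and cohorts without signals go no further.

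**Conclusion.** The trimming rule is wrong as written. It leaves the two groups on different score ranges and contradicts the section's own positivity and similarity aims. The RR and RD are biased wherever outcome risk varies with the propensity score. Some such variation is to be expected, because the score includes age, comorbidities, prior hospitalizations and long-term care residency while the outcomes include death, admission and sepsis.

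The null RR of about 0.99 to 0.78 rests on normal scores, a shift of 0.5 to 1.5 SD, a positive log-risk slope of 0.1 to 0.5 per SD, and no re-estimation of the score. The low end combines the largest separation with the steepest slope, where the balance criterion may exclude some cohorts. The consequence that later steps cannot repair is missed harm; false signals still face the matching check. The mechanism is certain from the text, the size is not.

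**What to change.** In the balancing section, exclude everyone, exposed or referent, whose score is below the exposed group's 1st percentile or above the referent group's 99th percentile. Then re-estimate the score, compute the ATT weights within that common range, and recheck balance. State that the estimand is the ATT in the trimmed exposed group. If the program already trims both groups, only the wording needs correcting.

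The cost is a small change in code and text, and about 1% more referents and up to 1% more exposed removed per cohort. Precision need not suffer, because the most extreme weights go. In the 20-covariate simulation with 10 referents per exposed and no re-estimation, the effective referent sample size per exposed rose from 3.6 to 4.7 at a shift of 1.0, and from 1.1 to 2.6 at 1.5.
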